#### Inclusion criteria

1) Patients with CIS aged between 18 and 55 years will be eligible for entry into the study if symptom onset occurred within 3 months of screening, they have two or more asymptomatic T2 lesions on MRI brain consistent with demyelination, not treated with steroids within 30 days of screening and are not on any other DMT.

2) Healthy control participants will be recruited from hospital staff, and will be aged between 20 and 40 years with a female:male ratio of 2:1, in line with the gender ratio seen with CIS.

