### Study endpoints

The primary endpoint is the effect of oral vitamin D at 5,000 and 10,000 IU/day compared with placebo on the frequency of CD4 T-cell subsets and cytokine responses in peripheral blood mononuclear cells in patients with CIS and in healthy control participants at weeks 16 and 24 compared with baseline.

Secondary endpoints include: the following. 1) In the patients with CIS having MRI brain scans at baseline and week 24, the number of new and enlarging T2 lesions and gadolinium-enhancing lesions at week 24 compared with baseline in patients receiving oral vitamin D at 5000 IU and 10,000 IU/ day compared with placebo, 2) In the patients with CIS, the effects of oral vitamin D at 5,000 and 10,000 IU/day compared with placebo on relapse occurrence, calculated as the annualized relapse rate (ARR), the percentage of patients who are relapse-free, and time to first relapse. 3) The effects of oral vitamin D at 5,000 and 10,000 IU/day compared with placebo on the percentage of treated patients with CIS who are free from any evidence of disease (clinical and MRI) activity.

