An enhancing new T2 lesion will be considered a single lesion. Two radiologists will together examine the MRI scans at baseline and week 24, without having knowledge of the treatment group to which the patient/participant belongs. The two radiologists will determine by consensus for each study subject the numbers of new and enhancing T2 lesions at week 24 weeks compared with baseline, and thus the cumulative total number of new lesions over the 24 week period. Mean and median T2 and gadolinium enhancing lesions will be assessed for each treatment allocation group at baseline and 24 weeks.

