### Sample size

The power calculations for this study were based on a pilot study, which examined immunologic outcomes in four healthy control participants treated with vitamin D 5,000 to 10,000 IU/day at our institution [32]. All calculations for numbers needed in the study were based on α = 5% and β = 80%. Based on flow cytometry analysis of T-cell subsets, the change in IL-17-producing CD4 T-cells (Th17 cells) had an effect size (mean ± SD) of 1.9 ± 1.8 indicating a need for five study subjects per group for 80% power. For IFN-γ-producing CD4 T-cells (Th1 cells), the effect size was 4.3 ± 6.3) indicating a need for 19 subjects per group for 80% power. The changes noted in cytokines in response to anti-CD3 stimulation of PBMC were 1) for IL-17, Δ = 44.5 ± 44.3, thus 10 participants needed in each group; 2) for IFN-γ, Δ = 32.8 ± 1.2, thus 6 needed in each group; and 3) for IL-10, Δ = −455 ± 27, thus number needed is < 5. The changes noted in cytokines in response to PPD stimulation were 1) for IFN-γ, Δ = 1860 ± 1835, thus 10 needed, in each group and 2) for IL-10, Δ = −576 ± 86, thus number needed is <5. On the basis of these results, at least 10 subjects should be included in each group (the only immunologic endpoint not powered would be the flow cytometry analysis of the IFN-γ-producing cells). Recruiting 39 healthy controls and 45 patients with CIS will allow for a drop-out rate of 20% and 30% respectively.

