### Statistical methods

All analyses assume a two-sided test of hypothesis with an overall α level of 0.05. Immunologic endpoints and *post hoc* analyses, which will include the 16 and 24 week endpoints, are considered exploratory, and will not be adjusted for multiple comparisons. Descriptive statistics will be presented as mean ± SD. Non-parametric tests will be used to compare characteristics between treatment groups. For outcomes, the sign/sign rank test will be used to evaluate continuous outcomes. McNemar testing will be used to categorize categorical and binary outcomes. For non-parametric testing on unpaired continuous data, the Wilcoxon rank sum test will be used. All outcomes will be adjusted for baseline serum 25(OH)D levels, and for mean serum levels achieved at weeks 16 and 24.

Missing data will be imputed as the mean of the preceding and following measurements. Only patients completing at least 4 months of full participation in the study or experiencing a relapse at any time in the study will be included in the final analysis. Non-adherent participants, defined as those with an increase in serum level of 25(OH)D of less than 50 nmol/l from baseline, will be excluded from the final analysis.

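### Immune outcomes are adjusted for 25(OH)D but not for their own baseline value, which costs precision in a small comparison with placebo

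*Protocol article*

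**What the plan says.** The Statistical methods section of the protocol article sets one adjustment rule: "All outcomes will be adjusted for baseline serum 25(OH)D levels, and for mean serum levels achieved at weeks 16 and 24". No other covariate is named. For continuous outcomes the section names the sign or signed-rank test, which works on paired differences. It names the Wilcoxon rank sum test for unpaired continuous data. It calls the immunologic endpoints exploratory.

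Under Study endpoints, the primary endpoint sets each vitamin D dose against placebo on CD4 T-cell subsets and cytokine responses at weeks 16 and 24 relative to baseline, in patients with CIS and in healthy controls. The MRI endpoint, for patients only, is "the number of new and enlarging T2 lesions and gadolinium-enhancing lesions at week 24 compared with baseline". The MRI section adds: "Mean and median T2 and gadolinium enhancing lesions will be assessed for each treatment allocation group at baseline and 24 weeks".

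On the stage of disease at entry, the inclusion criteria admit patients with CIS if "symptom onset occurred within 3 months of screening". The exclusion criteria rule out an exacerbation in the 6 weeks before entry.

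**The concern.** Expressing an outcome relative to baseline is not the same as adjusting for the baseline value. If baseline and follow-up correlate imperfectly, an arm that happens to start higher will tend to fall further with no treatment effect. The change score then carries part of that chance imbalance into the contrast. Separate randomization of patients and controls (Randomization section) keeps arm sizes equal, but nothing described there balances immune activity within either group.

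Two things are at stake. Arms are small, so sizeable imbalances are likely and any single result may be shifted by one. The change score is also the noisier analysis unless the correlation is high, in a trial with little precision to spare. A further risk comes from the choice of test. A paired test within each arm does not answer a question about placebo, and in recently affected patients it would also register any spontaneous recovery.

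**Working it through.** **Inputs from the protocol article.** "All analyses assume a two-sided test of hypothesis with an overall α level of 0.05". Power is 80%, and at least 10 evaluable participants are wanted per group (Sample size). The planning figures come from "four healthy control participants treated with vitamin D 5,000 to 10,000 IU/day". For anti-CD3 stimulation the article gives: "for IL-17, Δ = 44.5 ± 44.3, thus 10 participants needed in each group".

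**Assumptions.** The article gives no baseline to follow-up correlation r, so 0.3 to 0.9 is shown. Equal variances and normality are assumed, and ± 44.3 is read as the SD of the change.

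**1. The plan's own figure.** A paired t-test with effect 44.5/44.3, two-sided α of 0.05 and 80% power needs 9.9, so 10, as stated. Drop-out: 10/(1 − 0.2) = 12.5, so 13 × 3 = 39; 10/(1 − 0.3) = 14.3, so 15 × 3 = 45. Both match. For this outcome the target of 10 therefore fits a within-group change. A two-sample t-test on the same figures needs 17 per arm.

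**2. Chance imbalance.** The baseline difference between two arms of n has standard error √(2/n) SD: √(2/10) = 0.447, and 0.392 and 0.365 at n = 13 and 15. It exceeds 0.5 SD in 26%, 20% and 17% of trials.

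**3. Shift and variance.** Given a baseline imbalance d, the change-score contrast shifts by (1 − r)d in the opposite direction, an unadjusted follow-up contrast shifts by r·d, and ANCOVA by zero. In units of the outcome variance, the change score has 2(1 − r) and ANCOVA 1 − r², so the ratio is (1 + r)/2. At n = 10, estimating the slope from two arms multiplies the ANCOVA variance by about 1 + 1/(2n − 4) = 1.0625.

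**4. Numbers per arm for a comparison with placebo.** On change, 2 × (1.960 + 0.842)² × (44.3/44.5)² = 15.6, so 16 (17 by t). With the baseline covariate, multiply 15.6 by (1 + r)/2.

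| r (assumed) | Change-score shift at a one-SE imbalance, SD | Variance ratio, ANCOVA/change | Ratio with slope cost | n per arm with covariate (z) |
|---|---|---|---|---|
| 0.3 | 0.31 | 0.65 | 0.69 | 11 |
| 0.5 | 0.22 | 0.75 | 0.80 | 12 |
| 0.7 | 0.13 | 0.85 | 0.90 | 14 |
| 0.9 | 0.04 | 0.95 | 1.01 | 15 |

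The z-based numbers are slightly optimistic, as the step from 16 to 17 on change shows.

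**5. Does settling distort the result?** This was simulated with no treatment effect, 3,000 runs per setting, r of 0.3, 0.5 and 0.7, 10 or 15 per arm, and a common shift of 0, 0.5 or 1 SD in both arms.

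- Between arms, rank sum on change, rank sum on follow-up and ANCOVA all reject in 4 to 6% of runs, whatever the shift.
- Within one arm, the signed-rank test rejects in 21 to 43% (n = 10) and 32 to 61% (n = 15) at a shift of 0.5 SD, and in 64 to 99% at 1 SD.
- Significance in the active arm alone occurs in 17 to 25% at 0.5 SD.

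**The case against.** The strongest reply is that the trial is randomized against concurrent placebo. A reader might infer from the recent-onset entry criterion that recovery after the attack biases the treatment comparison. The documents do not support that. Recovery is shared by the arms and cancels in expectation, with or without a baseline covariate, and chance imbalance is already counted in the test's error rate. Step 5 confirms this. The argument also has no bearing on the 39 healthy controls. Where settling does mislead, through within-arm tests, the cure is to compare arms; a covariate alone would not do it.

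A reader might also infer that baseline immune and MRI data go unused. They do not: both enter as the reference for the endpoint. New and enlarging T2 lesions are counted against the baseline scan, so the change-score formula does not apply to them, and the article gives nothing from which to size an MRI gain.

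Finally, the article does not say that 25(OH)D is the only adjuster, it is a condensed account, and the endpoints are exploratory. That limits the weight of the point. But the rule is stated for all outcomes, so an analysis plan that followed it would omit the most useful covariate. Exploratory status is used in the article to waive multiplicity adjustment, which does not bear on precision. The named rank and McNemar tests take no covariates, so a model has to be specified in any case.

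One limit on the reply: cancellation holds for everyone randomized. The Statistical methods section excludes participants by duration of participation and by 25(OH)D rise, so balance among those analysed is not assured. Baseline adjustment would repair that only in part.

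**Conclusion.** The point holds as one of precision and conditional bias. With 10 evaluable per arm, a one-standard-error baseline imbalance shifts a change-score contrast by 0.31 to 0.13 SD for r from 0.3 to 0.7. Over that range ANCOVA needs 0.65 to 0.85 of the variance, or 0.69 to 0.90 after the cost of estimating the slope. At r = 0.9 the gain is negligible. For the IL-17 response to anti-CD3, a comparison with placebo on change needs 16 to 17 per arm, more than the 13 or 15 randomized; with the covariate about 11 to 14 would do for r of 0.3 to 0.7.

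Type I error of a between-arm comparison is not inflated. Settling after an attack is a threat only if within-arm signed-rank tests carry the conclusion, and only in patients with CIS. The sizes rest on the assumed r, equal variances and normality, and on a pilot of four people.

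**What to change.** Reword the Statistical methods section of the protocol article so that, for each immune measure at weeks 16 and 24:

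- each vitamin D arm is compared with placebo, separately in patients with CIS and in controls;
- the covariates are the measure's own baseline value and baseline 25(OH)D, in a rank-based or log-scale ANCOVA if the measure is skewed;
- 25(OH)D achieved at weeks 16 and 24 is left out of this model, because treatment raises it and conditioning on it can remove the effect being tested;
- within-arm sign or signed-rank results are descriptive only.

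Optionally, adjust the week 24 MRI counts for the baseline gadolinium-enhancing lesion count.

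The cost is one degree of freedom per covariate and a change of analysis wording. Baseline 25(OH)D is already planned, every value is already collected, and no extra participants or visits are needed.

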## Background

Multiple sclerosis (MS), a chronic inflammatory disease of the central nervous system, is the most common disabling neurologic disorder of young adults. The causes of MS remain unknown, but it is widely believed that there is interplay between genetic and environmental factors [1]. Evidence for the role of the environment in the development of MS is supported by a strong correlation between MS incidence/prevalence and increased latitude and lower levels of sun exposure, suggesting an association with vitamin D production [2-4]. Individuals who emigrate before the age of 15 years from an area of high MS prevalence to one of low prevalence, acquire the lower risk of MS in their new country of residence. Migration studies provide perhaps the strongest support for the role of environmental factor(s) in this disease [5,6].

People living at high latitudes are generally deficient in vitamin D, as measured by serum 25-hydroxyvitamin D (25(OH)D) levels [7,8]. In one study, mean winter 25(OH)D levels in healthy control subjects in Ireland were 36.4 nmol/l, and more patients with MS had vitamin D deficiency (serum 25(OH)D levels less than 25 nmol/l) compared with control subjects [9]. Patients have lower serum vitamin D levels during MS relapses, and also have blunted parathyroid hormone responses [10,11]. In 267 Dutch patients with relapsing remitting multiple sclerosis (RRMS), higher vitamin D levels were associated with an increased chance of remaining relapse-free [11]. In 134 North American patients with RRMS or clinically isolated syndrome (CIS) of pediatric onset, the strongest predictor of further relapse was the baseline serum vitamin D level [12]. In a prospective Australian study of 145 patients with RRMS, each increase of 10 nmol/l in baseline serum vitamin D level was associated with a 12% reduction in the risk of a further relapse [13]. Vitamin D deficiency may increase susceptibility to MS even *in utero*; higher maternal vitamin D intake during pregnancy was associated with a 38% lower risk of MS in offspring [14], and maternal vitamin D levels greater than 75 nmol/l were associated with a 61% reduced risk of MS in children [15]. Month of birth studies showing an increased MS incidence in those with spring versus autumn births also provide evidence of the role of maternal vitamin D [16].

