The potential therapeutic effect of vitamin D supplementation was first suggested by Goldberg in 1986 [17]. Dosing studies in healthy volunteers have shown that supplementation with vitamin D 10,000 IU daily results in an increase in serum 25(OH)D levels of 150 nmol/l over a 12 week period [18]. A Canadian phase I/II open-label, randomized, placebo-controlled trial (RCT) of 49 patients with RRMS who were randomized to placebo or escalating doses of vitamin D over a 52 week period showed a trend toward relapse reduction in the actively treated group [19]. This study was primarily aimed at establishing the safety and tolerability of high-dose vitamin D supplementation; the mean vitamin D dose was 14,000 IU per day, and there were no adverse events or hypercalcamia despite maximum mean vitamin D levels of 413 nmol/l being achieved. The results from this phase II trial [19], and from dosing [18] and observational studies [12,13], suggest that pharmacologic doses of vitamin D of up to 10,000 IU/day are safe, and may reduce the risk of relapse by a factor superior to the 30% reduction reported from the pivotal trials of interferons in RRMS [20,21].

Vitamin D modulates both the innate and adaptive immune systems [22]. The active metabolite, 1,25 (OH) vitamin D, primarily mediates its effects through the intracellular vitamin D receptor (VDR) [23], which is present in monocytes, dendritic cells, B-cells, and CD4+ T-cells [11,22]. Activation of VDR alters transcription, proliferation, and differentiation of immune cells [23], and modulates immune response both indirectly, by reducing the activation of pro-inflammatory T-cells by antigen-presenting cells [24], and directly, by inhibiting T-cell and B-cell proliferation [22,25]. This results in a T-helper (Th) 2-cell driven anti-inflammatory state [11,22,26].

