There is thus accumulating evidence that vitamin D deficiency increases susceptibility to MS, and that vitamin D supplementation reduces disease activity by immunomodulatory mechanisms. It seems probable that serum vitamin D levels of greater than 100 nmol/l are required to produce the immunologic effects of vitamin D and thus, in patients with MS with vitamin D deficiency, doses of 5,000 to 10,000 IU/day are needed to achieve this. Most patients with RRMS, once diagnosed, commence treatment with first-line disease-modifying therapies (DMTs). Several RCTs are underway to examine the effects of vitamin D supplementation in patients with RRMS already receiving first-line DMTs, using clinical and MRI outcomes [27,28]. In the UK and Ireland, patients with CIS are not usually commenced on DMTs until there is clinical or MRI evidence of dissemination in time. These CIS patients, at risk of developing RRMS, may be recruited into trials of potentially therapeutic agents in order to examine the efficacy of specific therapies in preventing the development of clinically definite MS [29]. We have therefore designed this RCT to examine, over a 24 week treatment period the effects on immunologic measures as a primary outcome, both in patients with CIS and in healthy control participants, randomized to either of two doses of vitamin D (5,000 or 10,000 IU) or to placebo. In addition, in the patients with CIS, clinical and MRI efficacy measures will be assessed as secondary outcomes.

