**Figure 1 F1:**
[figure not shown]
**Schematic diagram of study structure.** There are two study groups of subjects: 39 healthy control participants and 45 patients with clinically isolated syndrome (CIS). Each of the two groups will be randomly allocated to one of three blinded treatments: placebo, vitamin D 5,000 IU, or vitamin D 10,000 IU daily. Study duration is 24 weeks with immunologic testing (primary endpoint) of all study participants at baseline, week 16, and week 24. There will be 4-weekly clinic visits to assess safety measures and clinical status. 4 weeks after completion of the study there will be a follow-up safety visit. Magnetic resonance imaging will be carried out at baseline and week 24 in the CIS population only.

At all visits, study participants will have any changes in medical history or medications recorded, and will undergo a general physical and neurologic examination. Patients with CIS will be assessed for any evidence of relapse, defined as the appearance of a new neurologic abnormality or reappearance of a previously seen neurologic abnormality, separated by at least 30 days from the onset of the preceding event. The abnormality must be present for at least 24 hours, must be based on objective clinical evidence, and must occur in the absence of fever or known infection.

Blood biochemistry, including liver function tests, electrolytes, urea, creatinine, and serum calcium will be measured at all study visits.

Serum vitamin D levels and parathormone levels will be assessed at baseline, and at weeks 4, 8, 12, 16 and 24. Serum 25(OH)D levels will be measured by liquid chromatography-mass spectrometry. Intact parathormone levels will be measured by a two-step sandwich immunoassay using chemiluminescence technology.

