## Discussion

Supplemental vitamin D appears to have potential as a therapeutic agent for MS; what is less clear is the optimal dose of vitamin D needed to effect change within the immune system. Our study is designed to address this question, and to add to the growing evidence of the safety and tolerability of high-dose vitamin D supplementation. As this is a phase II randomized, placebo-controlled trial with two distinct study groups and is adequately powered to meet the primary endpoint, it should be considered a high-quality trial aiming to provide class II evidence of the primary endpoint.

Existing guidelines on vitamin D supplementation are conservative, and refer mainly to bone health [33], with 4,000 IU considered the upper limit of tolerability, despite the fact that sun exposure can provide an adult with up to 20,000 IU per day [34]. Older adults are now advised to sustain 25(OH) D concentrations of greater than 75 nmol/l for optimal bone health and, in order to achieve that, they need to consume approximately 4,000 IU/day of vitamin D [18,35]. Levels greater than 100 nmol/l are needed to ensure that patients are receiving adequate immunomodulating doses of vitamin D. Based on previous dosing studies [18], the maximum serum 25(OH)D level expected with a daily dose of 10,000 IU is approximately 250 nmol/l, making both treatment doses safe and tolerable.

The availability of DMT and the earlier recognition and diagnosis of MS have a significant effect on trial design for the evaluation of new drugs, and this also raises ethical concerns. Most would feel that placebo-controlled studies of the RRMS population are unethical. This results in the need for large multicenter trials to achieve adequate numbers to power the study over longer time periods to assess for clinical endpoints. Thus, costs are generally prohibitive and really limits these studies to large pharmaceutical companies.

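### Adjusting every outcome for the 25(OH)D level achieved on treatment conditions on the mediator and removes the effect that the trial sets out to estimate

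*Protocol article*

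**What the plan says.** Under Statistical methods, the protocol article commits to one covariate rule for the whole trial: "All outcomes will be adjusted for baseline serum 25(OH)D levels, and for mean serum levels achieved at weeks 16 and 24". The rule is not confined to a secondary or mechanistic analysis, and the text shown describes no analysis adjusted for baseline alone.

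Under Study endpoints, the target is the randomized contrast: "The primary endpoint is the effect of oral vitamin D at 5,000 and 10,000 IU/day compared with placebo".

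The article also sets out how it expects the treatment to work:

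- Dose raises serum level (Background): "supplementation with vitamin D 10,000 IU daily results in an increase in serum 25(OH)D levels of 150 nmol/l over a 12 week period".
- Serum level drives the immune effect (Background): "It seems probable that serum vitamin D levels of greater than 100 nmol/l are required to produce the immunologic effects of vitamin D". The Discussion repeats this: "Levels greater than 100 nmol/l are needed to ensure that patients are receiving adequate immunomodulating doses of vitamin D".

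The visit schedule has 25(OH)D measured at baseline and then on treatment, including weeks 16 and 24. The two achieved values are therefore taken after randomization.

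**The concern.** A covariate in a randomized comparison should be fixed before treatment can influence it. Baseline 25(OH)D meets that condition. The level at weeks 16 and 24 does not, because it is what the dose is given to change. Three consequences follow.

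1. **The question changes.** The adjusted coefficient compares people on different doses who reached the same serum level. That is the part of the dose effect that bypasses serum 25(OH)D, which on the article's own rationale should be little or nothing. A dose that works as hypothesized could be reported as having no effect.
2. **Randomization no longer protects the comparison.** Placebo and 10,000 IU participants with the same achieved level differ in whatever produced that level, such as adherence, sun exposure or body mass. If those factors also affect the outcome, the adjustment introduces confounding that the unadjusted comparison does not have.
3. **Precision collapses.** Achieved level almost identifies the arm, so the model has little information left with which to separate the two.

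The rule covers all outcomes, so the MRI and relapse endpoints are affected as well as the immunologic ones.

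**Working it through.** **Inputs from the article**

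- Rise in 25(OH)D at 10,000 IU/day: 150 nmol/l (Background).
- Untreated level: 36.4 nmol/l, from the winter mean in Irish healthy controls (Background).
- Effect size: the pilot changes under Sample size give 44.5/44.3 = 1.00 SD (anti-CD3 IL-17) and 1860/1835 = 1.01 SD (PPD IFN-γ). I use 1.0 SD.
- Numbers: at least 10 evaluable per group; enrolment 39/3 = 13 and 45/3 = 15 per arm.
- Two-sided α of 0.05.

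**Assumptions, not in the article**

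- Rise at 5,000 IU/day of 75 nmol/l (half of 150).
- Baseline SD of 15 nmol/l.
- Within-arm SD of the rise between 20 and 50 nmol/l.
- A linear model, since the article does not say how the adjustment enters.

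**The plan's own figure.** A paired (one-sample) t-test at 80% power gives 10 for both pilot effects above, as stated. Inflating for drop-out, 10/(1 − 0.20) = 12.5, so 13 × 3 = 39; and 10/(1 − 0.30) = 14.3, so 15 × 3 = 45. Both totals reproduce.

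**Collinearity.** For the 10,000 IU versus placebo contrast with n per arm, adding the achieved level multiplies the variance by

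1 + [D²/(k·n·SD²)]/(2/n) = 1 + D²/(2k·SD²),

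where D = 150 is the difference in mean rise and k is the number of arms in the model.

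| Within-arm SD | Two arms, k = 2 | Three arms, k = 3 |
|---|---|---|
| 20 | 15.1 | 10.4 |
| 30 | 7.25 | 5.2 |
| 40 | 4.5 | 3.3 |

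At SD 30 the two arm means are 150/30 = 5 SDs apart, so almost no participants on different arms share an achieved level.

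**Bias and power.** Three arms; 10, 13 and 15 per arm; SD 20, 35 and 50; 2,000 runs per setting; true effect of 10,000 IU versus placebo 1.0 SD.

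Adjusted for baseline 25(OH)D only, under full mediation, the estimate is 0.99 to 1.02 SD. Power is 51-57% with 10 per arm, 63-67% with 13 and 70-74% with 15.

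With the achieved level added:

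| Share acting through serum level | Estimate (SD) | Rejection rate |
|---|---|---|
| 100% | −0.07 to 0.02 | 4-6% |
| 75% | 0.20 to 0.30 | 5-7% |
| 50% | 0.48 to 0.55 | 6-13% |
| 0% | 0.95 to 1.03 | 9-38% |

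In the last row there is nothing to remove, yet the empirical standard error is about 1.6 to 3.5 times larger than without the term. Power falls to 9-38% from 54-75%.

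**Sensitivity to the linear form.** The article's rationale reads more like a threshold at 100 nmol/l. With a 1.0 SD step at that level, 10 per arm and SD 20 to 40, the linearly adjusted estimate is about 0.2 to 0.3 SD in three arms, with rejection of 5-7%. In a model of only the 10,000 IU and placebo arms it is about 1.0, 0.8 and 0.6 SD at SD 20, 30 and 40, with rejection of 7-10%. The balance between bias and imprecision shifts, but the loss of power does not go away.

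**The case against.** Several points can fairly be made for the plan.

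- **Complete removal is conditional.** It needs full mediation and a correctly modelled covariate. This stands: with partial mediation the direct part survives, and with a threshold effect the bias can be smaller. But no setting examined favours the adjustment, because each one brings bias, severe imprecision or both.
- **The analysis modelled here is not specified.** The tests the article names (sign or signed rank, McNemar, Wilcoxon rank sum) take no covariates. This stands as a reason to treat the figures as illustrative. It does not withdraw the sentence, which still says that all outcomes will be adjusted.
- **The immunologic endpoints are labelled exploratory.** In the text that label serves to justify leaving multiple comparisons unadjusted. It does not repair a biased contrast, and the Discussion presents the trial as adequately powered for its primary endpoint.
- **The authors may have meant an exposure-response analysis.** That would be reasonable, but the text does not say so.
- **The shortfall from 80% power before adjustment is not due to this rule.** Correct. The stated 10 per group comes from a within-person calculation, whereas the contrast here is between arms. Only the further drop after the achieved level is added belongs to this point.

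A full analysis plan could add detail on method. The objection here, however, is to an explicit commitment and not to an omission.

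**Conclusion.** The concern holds, and the sentence should be corrected before the analysis. As written, the rule conditions the dose-versus-placebo comparison on a post-randomization variable that the article places on the causal path.

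If the trial's hypothesis is right and the effect runs through serum 25(OH)D linearly, a true 1.0 SD effect is estimated as about zero and detected no more often than chance. If half runs through serum level, about half the effect is lost and the rejection rate is 6-13%. If none does, the estimate is unbiased but power is at best 38% in the settings examined.

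The exact sizes rest on the assumed within-arm SD, the assumed 5,000 IU rise and the linear model. The full-mediation result of about zero held at every within-arm SD from 20 to 50 nmol/l. Adjusting for baseline 25(OH)D is not in question.

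**What to change.** In Statistical methods, delete the adjustment for levels achieved at weeks 16 and 24. State that the main analysis of every outcome compares the randomized arms, adjusted only for values fixed before randomization: baseline 25(OH)D and, preferably, the participant's own baseline value of the outcome where one exists. The second covariate is an improvement and is not essential to the correction.

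If the relation between achieved 25(OH)D and outcome is of interest, describe it as a separate, labelled exploratory exposure-response analysis. Say that it is not a randomized comparison and may be confounded by adherence, sun exposure and body mass.

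The cost is one revised sentence and, if wanted, one added. No further data, visits or participants are needed. The change should be made before unblinding.
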